### Randomisation

After recruitment, teams are randomised to intervention or control condition. To ensure comparability of teams in the intervention and control arm, clusters of comparable teams are made based on health care organisation, level of intensity of care (long-term residential or long-term clinical care), caseload size and location (urban or rural). Each cluster consists of two comparable teams in terms of these variables; one cluster contains five comparable teams. Of each cluster, the teams are randomly allocated to one of the two conditions by a computerised random number generator. A research nurse not involved in the study reveals the results of the allocation. All participating teams are randomised simultaneously making allocation sequence concealment unnecessary.

Blinding of teams and patients to the allocation condition is not possible due to the nature of the intervention. Research nurses assessing the outcomes in the ROM screenings are blinded to the intervention allocation. The research assistants taking the six-minute walk test, body fat test and lifestyle questionnaires in patients and staff are not blinded to the intervention at the baseline and 3 months measurements. Outcome measures at 12 months after baseline are however carried out by different research assistants that are not informed of the allocation status of the teams and patients. All post-intervention measures at 12 months after start of the intervention will thus be obtained blinded.

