Description of tasks and schedule of ELIPS intervention:*-1 - 0 months Preparation phase*Lifestyle coaches visit intervention teams to become acquainted with the team, patients and location.Lifestyle coaches explore which (un)healthy behaviours and activities take place.Lifestyle coaches inquire which lifestyle activities patients and teams prefer and examine logistic possibilities for these activities.Lifestyle coaches create a team-specific lifestyle plan based on ELIPS lifestyle goals, structured protocols and the preferences and possibilities of the team and patients.Baseline measures: ROM-nurses carry out ROM measurements, research assistants carry out additional measures. See Table 2 for an overview of measurements.*0 - 3 months Implementation phase*Lifestyle coaches organise lifestyle activities and workshops. The team is involved in the organisation and motivates patients to participate. Lifestyle coaches first demonstrate the activities, then co-organise them out together with the team, while towards the end, they supervise team members who, over time, are made responsible for carrying out the lifestyle activities themselves.Lifestyle coaches transfer their knowledge and skills of healthy behaviours to the team.Lifestyle coaches assist the team in setting concrete goals in order to improve or maintain a healthier lifestyle after the lifestyle coaches have gone.Structural changes to adjust the obesogenic environment are explored and implemented.*3 - 12 months Monitoring phase*3-months measures: ROM-nurses carry out ROM measurements, research assistants carry out additional measures. See Table 2 for an overview of measurements.Team continues lifestyle activities, aiming to achieve the pre-defined goals.Start monthly monitoring visits. A lifestyle coach evaluates with the team the pre-defined goals, detects obstacles in achieving these goals, solves observed obstacles. If necessary, recommendations for improvements are made.12-months measures: ROM-nurses carry out ROM measurements, research assistants carry out additional measures. See Table 2 for an overview of measurements.12-months monitoring visit: final monitoring wherein goals are evaluated and recommendations are made to sustain the lifestyle activities.

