**Measurements on team level**					
General information	Age, gender, birth year, level of education, number of years working in psychiatry, function*	X	X		X
Process evaluation	Semi-structured interview team leader*	X	X	X**	X
	Semi-structured interview staff*	X	X	X**	X
	Semi-structured interview patients*	X	X	X**	X
	Observatory list*	X	X	X**	X
Staff questionnaire	Knowledge on diet and physical activity, attitude towards lifestyle changes in patients, self-efficacy in addressing lifestyle issues with patients*	X	X		X

*Measurement is not part of ROM screening. Additional measures are collected by research assistants.

**Measures are collected at intervention teams only.

Some measurements are not part of ROM and will be carried out by research assistants, mostly the lifestyle coaches. Research assistants will receive one day training to study protocols and procedures and to practice assessing the functional physical fitness in patients with the six-minute walk test, assessing the body fat percentage with the Bioelectrical impedance analysis, measuring height and weight, assessing food habits with a food questionnaire based on Dutch guidelines for a healthy diet which is adapted to this population, and questionnaires and interviews with patients and staff for process evaluation. All measurements will be taken on site or in a location that is familiar to the patient (e.g. patient’s own room, nurses’ office). Research assistants contact patients directly to set up an appointment or staff members act as intermediaries to facilitate setting up appointments. Appointments for interviews with staff members are scheduled by research assistants and staff members.

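### Randomising all teams at once protects the team assignment, but allocation is known before or during baseline, so patient participation and the coach-run baseline tests are unprotected

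*Protocol article*

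**What the plan says.** All references are to the protocol article.

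- **Randomisation:** "After recruitment, teams are randomised to intervention or control condition", and "All participating teams are randomised simultaneously making allocation sequence concealment unnecessary". A research nurse who is not involved in the study reveals the result.
- **Intervention, task schedule, month -1 to 0:** "Lifestyle coaches visit intervention teams to become acquainted with the team, patients and location". The same block lists "Baseline measures: ROM-nurses carry out ROM measurements, research assistants carry out additional measures".
- **Outcomes, text after Table 2:** "Some measurements are not part of ROM and will be carried out by research assistants, mostly the lifestyle coaches".
- **Randomisation, on blinding:** "Blinding of teams and patients to the allocation condition is not possible due to the nature of the intervention". The assistants who take the walk test, the body fat test and the lifestyle questionnaires "are not blinded to the intervention at the baseline and 3 months measurements". For the routine outcome monitoring (ROM), which includes waist: "Research nurses assessing the outcomes in the ROM screenings are blinded to the intervention allocation".
- **Participants:** patients who do not take part in ROM are left out of the analysis.
- **Sample size:** there are about 1000 eligible patients, and a pilot suggests that two thirds will be measured successfully.
- **Statistical methods:** the models adjust for baseline, and secondary outcomes are analysed in the same way as waist.

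**The concern.** In a cluster trial, two things can go wrong once allocation is known, and simultaneous randomisation prevents neither.

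The first is who takes part. Staff who know their team's arm may encourage attendance differently, and patients who have met a coach may respond differently from those who have not. Intention-to-treat analysis cannot bring back patients who never entered. Baseline adjustment deals with a difference in measured waist, but not with a difference in motivation.

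The second is what is recorded at baseline. If the assessor knows the arm, an error that differs between arms is carried into every model that adjusts for that baseline, even where the 12-month assessment is blinded.

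The protocol's sentence treats concealment as fully dealt with, and so gives no reason to protect either step.

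**Working it through.** **Step 1. Order of events.**

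| Event | Where stated | Timing relative to allocation |
|---|---|---|
| Teams recruited | Randomisation | Before |
| Teams randomised together, result revealed | Randomisation | – |
| Coaches visit intervention teams | Task schedule, month -1 to 0 | After; otherwise there are no intervention teams to visit |
| Baseline measures | Task schedule, month -1 to 0 | Same month as the coaches' visits |
| Non-ROM baseline assessors know the arm | Randomisation | Consistent only with allocation before baseline |
| Patient signs consent | Mentioned under Sample size | No date given |

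Allocation is therefore known to teams, patients, coaches and non-ROM assessors before or during baseline. The point at which patients agree to take part is not fixed.

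**Step 2. How much participation is open.** Expected to be measured: 2/3 × 1000 ≈ 667. Not expected to be measured: 1000 − 667 ≈ 333. The protocol does not say how many of the 333 would refuse and how many would agree but not be measured successfully, so 333 is an upper figure for the group in which selection could act. Access to patients runs partly through people who know the arm: team coordinators may set ROM schedules, and staff may arrange appointments for the assistants (Outcomes).

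**Step 3. Which outcomes are exposed to which problem.**

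| Outcome | Baseline assessor | Participation can depend on arm | Baseline value can depend on arm through the assessor |
|---|---|---|---|
| Waist (primary) and other ROM measures | ROM nurse, stated to be blinded | Yes | Not through the nurse, if blinding holds |
| Six-minute walk, body fat, SQUASH, food questionnaire | Unblinded assistant, mostly a coach | Yes | Yes |

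For the second row, suppose the baseline error differs between arms by δ and the fitted slope on baseline is β. The adjusted treatment effect is then shifted by −β × δ. Blinding at 12 months does not remove this term. The document gives neither β nor δ.

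**Step 4. Illustration for waist (assumed inputs, not an estimate).** Let knowledge of the arm add d percentage points to a participation of 66.7% in one arm. Let the added patients' waist change differ from the others' by 3 percentage points (assumed). Their share of that arm is s = d / (66.7 + d), and the bias is s × 3.

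- d = 5: 5/71.7 = 7.0%; bias 0.21 points; 0.21/5 = 4% of the 5% target effect
- d = 10: 10/76.7 = 13.0%; bias 0.39 points; 8% of the target
- d = 20: 20/86.7 = 23.1%; bias 0.69 points; 14% of the target

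Neither d nor the 3 points has a source in the protocol, and the direction could go either way. The figures show only that, on inputs like these, the effect would be modest rather than dominant.

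**The case against.** The case on the other side is substantial.

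- **The sentence is true as written.** It speaks of the allocation sequence, and teams that are all recruited first and then randomised together cannot be enrolled with foreknowledge. This stands. The defect is what the sentence leaves uncovered.
- **Recruitment may include patients.** The Randomisation section puts randomisation after recruitment, which could cover patient consent, and a condensed article may leave dates to the full protocol. A reader might infer that patients are shown to decide after learning their arm; the document does not say so. But the recruitment sentence concerns teams. The schedule, which the article does give, still places baseline in the coaches' month with unblinded assistants.
- **Waist is well protected as a measurement.** It is taken in duplicate under standard procedures by nurses stated to be blinded, at a regular yearly screening. Consent for research use of ROM data was asked for when ROM was introduced. A reader might infer that the waist baseline itself is contaminated; the document does not support that. What remains is attendance at the screening, which the earlier consent does not settle.
- **Coaches only prepare in that month.** They get acquainted, explore and plan, and activities begin at month 0. A reader might infer that the intervention is already being delivered at baseline; the schedule does not show that. Preparation visits are nevertheless enough to make the arm known.
- **All patients are invited, and baseline comparability is checked.** This reduces the risk. Equal invitation is not equal participation, however, and a check among participants cannot show unmeasured differences.

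**Conclusion.** The point holds in a limited form. Simultaneous randomisation secures the assignment of teams. It does not secure patient participation or baseline assessment, and the protocol's own schedule has both taking place when the arm is, or may be, known.

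For waist, the exposure is arm-dependent participation only. That is a risk, not a documented fact. Its size cannot be derived from the document, and the 0.2 to 0.7 points above rest entirely on assumed inputs. The conclusion for waist also relies on the nurses' blinding holding in practice.

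For the six-minute walk, body fat, SQUASH and food questionnaire the problem is firmer, because the protocol itself states that these baselines are taken unblinded, and the models then adjust for them.

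This should be corrected, since following the stated schedule produces the weakness and the remedy is mainly a change of order. It does not by itself invalidate the primary analysis.

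**What to change.** 1. Limit the statement on concealment to the team-level sequence.
2. In all participating teams, freeze the roster of eligible patients and the consent list before the research nurse reveals the allocation. Define the analysis population from that list, so that later attendance does not decide who is analysed.
3. Take the non-ROM baseline tests before the reveal, and start the coaches' preparation visits after it. The same assistants can then do the baseline tests without knowing the arm.
4. Where a baseline measure cannot be finished before the reveal, report participation by arm against all eligible patients, and compare participants with non-participants within each arm.

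**Cost.** The reveal is already a separate step, so this is mainly a reordering. It is not free: baseline covers roughly 667 patients, the coaches' start may move by more than a month, and teams measured early will have a longer gap between baseline and start. If that gap is unacceptable, freezing the roster and consent list is the part to keep, because it closes the participation route for all outcomes, including waist.

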### Measurements on patient level

Patient measurements include cardiometabolic health, disease history, medication use, mental health, psychosocial functioning, quality of life, lifestyle habits, care consumption and general information (i.e. age, gender).

Cardiometabolic health. The physical measurements include waist circumference, height, weight, pulse and systolic and diastolic blood pressure. Patients visit a (hospital) laboratory that collects a blood sample, if possible in fasting state for levels of lipids (total cholesterol, LDL-cholesterol, HDL-cholesterol and triglycerides), glucose metabolism (glucose, HbA1c) and clinical parameters (i.e. CRP, ALAT, ASAT, urea, creatinine, TSH, leukocytes) and vitamin D status. Measurements are taken following standard ROM protocols. Waist circumference is measured in duplicate using a flexible nonstretching tape halfway between the iliac crest and lowest rib in standing position at the end of an expiration. Weight is measured by calibrated scales (Seca, model 813) in light clothing without shoes or jackets. Measurements for height will be available from multiple measurements of both ROM nurses and research assistants. The highest height will be used unless patients wear shoes, then the highest height without shoes is used. Pulse and systolic and diastolic blood pressure are measured after 5 minutes’ rest in sitting position, using a blood pressure monitor (BOSO medicus control). Body fat percentage is measured in standing position [23] by bioelectrical impedance analysis (BIA) in triplicate using a single-frequency bioimpedance analyzer (Model BIA 101, AKERN Srl, Italy) [24,25].

Mental health. During an interview, trained nurses administer the PANSS (Positive and Negative Syndrome Scale, [26]) and the CDSS (Calgarary Depression Scale for Schizophrenia, [27]). Prior to the interview, patients fill in the MANSA, a self-report questionnaire about patients’ Quality of Life [28] and uncertainties can be discussed during the interview. The HoNOS (Health of the Nations Outcome Scale, [29]) is an observation scale of psycho-social functioning and is scored by the case manager or team.

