Lifestyle habits. Functional physical fitness is assessed by research assistants with a detailed protocol for the six-minute walk test [30], which contains standard phrases and time points for encouragement and has been validated in patients with schizophrenia [31]. The intraclass correlation coefficient was 0.96. Although a mild practice effect was detected for a three-day interval, this is unlikely to persist for a three–month interval. The test is conducted indoors. Patient staff is allowed to walk along with patients if necessary. Daily physical activity is assessed using the Dutch validated SQUASH questionnaire [32]. Nutritional habits are estimated using a semi-quantitative food frequency questionnaire with items based on a screening questionnaire for healthy eating habits of the Netherlands Nutrition Center according to the Dutch guidelines for a healthy diet [33] and adapted to this population. The questionnaire will be used to assess changes in dietary habits on food group level. It is not specifically validated in SMI patients and can and will not be used to derive quantitative estimates of total energy, macro- or micronutrient intake.

Cost-effectiveness parameters. Care consumption is estimated with the Dutch care consumption questionnaire [34], which is adapted to the context of the current study. Quality adjusted life years (QALYs) will be the primary outcome measure in the cost-effectiveness analysis. In order to estimate QALYs, utility scores will be derived from the SF12, using the SF6D algorithm [35,36].

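### The protocol says all 12-month measures are obtained blinded, but HoNOS is scored by the unblinded case manager or team, and several other 12-month outcomes rest on answers from unblinded patients or staff

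*Protocol article*

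**What the plan says.** The Randomisation section of the protocol article makes four statements about blinding:

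- For those treated and those treating: "Blinding of teams and patients to the allocation condition is not possible due to the nature of the intervention".
- The nurses who assess outcomes in the routine outcome monitoring (ROM) screenings are blinded.
- The research assistants who take the walk test, body fat and the lifestyle questionnaires "are not blinded to the intervention at the baseline and 3 months measurements". At 12 months other assistants, not told the allocation, take over.
- From this it concludes: "All post-intervention measures at 12 months after start of the intervention will thus be obtained blinded".

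The section on patient-level measurements says who supplies the data. HoNOS "is an observation scale of psycho-social functioning and is scored by the case manager or team". For quality of life, "patients fill in the MANSA, a self-report questionnaire". For activity, "Daily physical activity is assessed using the Dutch validated SQUASH questionnaire". For the cost-utility analysis, "utility scores will be derived from the SF12, using the SF6D algorithm".

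The Outcomes section, in the text after Table 2, adds that the measures outside ROM "will be carried out by research assistants, mostly the lifestyle coaches". The Intervention section says lifestyle coaches implement the intervention. The Statistical methods section analyses the secondary outcomes by the same mixed model as waist circumference.

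**The concern.** The word 'thus' in the blinding conclusion rests on two premises: blinded ROM nurses, and new, uninformed assistants at 12 months. Neither covers an outcome whose score comes from someone else. The team is the unit that was randomised. In the intervention arm it runs the lifestyle activities from month 3 to month 12 towards goals it set itself, so when it scores HoNOS it knows the arm and has a stake in the result. Because HoNOS belongs to the ROM battery, a reader could easily assume that the sentence on nurse blinding covers it.

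At stake is how results on functioning, quality of life, self-reported activity and QALYs are presented. If the sentence is carried into the report, a difference open to rater or reporting bias would be described as a blinded finding.

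A related, lesser matter is that the assessors of the non-ROM measures change between 3 and 12 months, and their blinding status changes with them. The trial's central argument is that effects last after the coaches leave, so the contrast between the two visits will attract attention.

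**Working it through.** No arithmetic on effect or power applies. The check is to set out, for each measure, who determines the recorded value and whether that person is blinded at 12 months.

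| Measure | Who determines the value | Blinded at 12 months? |
|---|---|---|
| Waist, blood pressure, PANSS, CDSS | ROM nurse | Yes, as stated |
| Lipids, glucose, other blood values | Laboratory | Not open to rating by team or patient |
| Walk test, body fat | Research assistant | Yes, as stated (uninformed assistants) |
| HoNOS | Case manager or team | No |
| MANSA | Patient | No |
| SQUASH | Patient | No |
| Care consumption questionnaire | Patient | No |
| SF12/SF6D | Patient | No |
| Staff questionnaire | Team members | No |

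The first two columns come from the sections on patient-level and team-level measurements, the third from the Randomisation section.

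**Schedule.** Table 2 marks HoNOS, MANSA, SQUASH, care consumption, SF6D and the staff questionnaire at 12 months. That is 1 scale scored by staff + 4 patient instruments + 1 staff instrument = 6 for which 'all' does not hold in the sense of a blinded source. The food frequency questionnaire would be a seventh. Its row in Table 2 carries no time marks, although the Outcomes section says in general that measurements take place at baseline, 3 and 12 months.

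**HoNOS.** Step 1: teams cannot be blinded. Step 2: the case manager or team scores HoNOS. Step 3: HoNOS is due at 12 months. It follows that at least one 12-month measure is not obtained blinded, and it is the instrument named for a stated objective, psycho-social functioning.

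**Patient and staff instruments.** An uninformed person handing out or collecting a form does not blind the person answering it. The recorded value therefore comes from an unblinded source at every visit. This includes the SF12, whose utilities give the QALY, the outcome named as primary for the cost-effectiveness analysis.

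**3 months.** The assistants are stated to be unblinded at that visit and elsewhere are said to be mostly the coaches. So for the walk test and the assistant-collected questionnaires, visit is confounded with assessor and with assessor blinding. A gain at 3 months that is smaller at 12 months could reflect a faded effect, a changed assessor, or both.

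**The case against.** The best reply is that 'obtained' refers to data collectors. The section first says openly that patients and teams cannot be blinded, then describes who collects the data, then concludes. Read that way, the sentence means only that uninformed people gather the 12-month data, and unblinded respondents are unavoidable in a team-level intervention. This has force for MANSA, SQUASH, care consumption and SF12, where it turns a contradiction into an ambiguity. It does not help HoNOS, where the case manager or team is the assessor.

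Four stronger readings are tempting, and the document does not support them.

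- **That the primary result is compromised.** Waist circumference is a ROM measure taken by nurses stated to be blinded at every visit.
- **That blinding at 3 months is misrepresented.** The article says plainly that the assistants are unblinded then. It claims no blinding for 3-month fitness, and the 12-month walk test is taken by uninformed assistants.
- **That coaches measure the teams they coached.** The text says only that the assistants are mostly coaches. It does not say which teams they measure.
- **That 3-month secondary results should become descriptive.** The objectives name both visits, and the step would not cure SQUASH or diet, which are still self-reported at 12 months.

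Safeguards also count. The walk test has a detailed protocol with scripted encouragement, and body fat is read from an analyser in triplicate. These limit assessor influence at 3 months; for the effort-dependent walk test they do not exclude it.

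**Conclusion.** The blinding conclusion is wrong as written. For HoNOS it contradicts the article's own account of who scores the scale. For the other five instruments scheduled at 12 months it can be defended only as a statement about data collectors, and it should say so. The consequence is confined to secondary, cost-effectiveness and team-level outcomes: functioning, quality of life, self-reported activity, care consumption, QALYs, and staff knowledge and attitudes. Waist circumference, blood pressure, laboratory values, PANSS and CDSS are unaffected as documented. The direction and size of any bias cannot be derived from the document.

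The 3-month assessment is a disclosed design weakness that calls for careful interpretation, not a correction of fact.

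This rests on three assumptions: the case manager is one of the care staff who cannot be blinded; SQUASH, care consumption and SF12 are answered by the patient, as their placing among patient-level measures suggests; and the stated blinding of ROM nurses and 12-month assistants is kept in practice.

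**What to change.** 1. Replace the sentence with one limited to the ROM-nurse measures (waist, blood pressure, PANSS, CDSS), laboratory values, and the 12-month walk test and body fat taken by uninformed assistants.
2. Name HoNOS and all patient and staff self-reports, including the QALY outcome, as unblinded. Carry that label into the results tables and the conclusions.
3. At 3 months, where the existing rota allows, arrange that no coach measures a team he or she coached. This does not make the assessor blind, but it separates delivery from measurement within a team.
4. State in advance that differences between 3 and 12 months in the walk test and lifestyle questionnaires will be interpreted in light of the change of assessor and of blinding status. The 3-month results keep their inferential status.

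Items 1, 2 and 4 cost only wording. Item 3 costs some rescheduling among existing assistants; if it is no longer feasible, item 4 remains. Sample size, the model and the primary analysis do not change.
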